## Study outcomes and analytic methods

The primary analytic approach is intention to treat with children in the clusters in the intervention arm considered exposed to the intervention. Data for all of the primary and secondary outcome variables will be captured on the routine treatment recording forms and all consultations for fever, pneumonia and diarrhea routinely completed by drug shop vendors/private clinics. The outcome of referral will be recorded on the referral forms by health staff for referred sick children presenting to health facilities with a referral form. The primary trial outcome is the proportion of sick children referred from a private outlet that complete referral (seen at higher level facilities). The denominator includes all referrals of sick children with a history of fever, pneumonia and diarrhoea. Through review of records at the private health facilities, care takers whose children are referred in a specific period of time will be followed up in their respective communities to verify whether they took up referral. Secondary outcomes are; appropriate case management for malaria, pneumonia and diarrhea among children and factors which influence referral or non-referral of sick children from the private sector. Other outcomes include the proportion of sick children seeking care at private outlets within 24 h of onset of symptoms, and time between consultations at private outlets and uptake of referral at health facilities (referral facilities).

A cluster-level approach to the analysis will be used due to the small number of clusters per arm [17]. The proportion relating to this primary outcome will be calculated in each cluster. If the distribution of the proportions in each study arm is skewed a logarithmic transformation will be applied and the geometric mean proportions computed. To compare the intervention with the control arm point estimates based on these cluster summaries will be used to derive risk differences; using a weighted average of the cluster proportions, with weights proportional to the sample size for each cluster, since consultation rates differ between drug shops/private clinics and clusters. If the data have been log transformed, this will be the ratios of the geometric means. Corresponding 95 % confidence intervals will be computed assuming separate estimates of the variances in the two study arms, or if log transformed using an estimate of the pooled standard deviation of the log-transformed cluster summaries. The null hypothesis that there is no intervention effect will be tested using an unpaired *t*-test. Finally, an estimate of the coefficient of variation, *k*, will be provided. The overall mean proportion of sick children referred in the intervention arm, with 95 % confidence interval, will be computed using a random effects model to account for cluster sample. This analysis will be restricted to data from the treatment records of registered drug shop/private clinics enrolled in the intervention arm of the trial. A two-stage process will be carried out to adjust for covariates. At the first stage a regression model will be fitted incorporating the covariate(s) of interest, except the study arm. Expected values from this model will be compared with observed values by computing a residual, based on the difference between observed and expected, for each cluster. In the second stage, adjusted risk differences and 95 % CIs will be estimated as described above, replacing the cluster-level proportions with the covariate adjusted residuals. The covariates that will be adjusted for include balance criteria used in randomization at cluster level (primary endpoint at baseline); level of qualification, number of years working as a drug shop vendor/private clinic and/or health worker; age of sick child, education level of caretaker, and occupation of caretaker. A test for interaction will be carried out, and a 95 % confidence interval computed, using the methods of [18]. The above methods will also be used to analyse the other secondary outcomes; appropriate case management for malaria, pneumonia and diarrhea among children in the private sector and time between consultations at private outlets and uptake of referral at health facilities (referral facilities).

Factors which influence the referral or non-referral of sick children from the private sector will be explored through focus group discussions and key informant interviews. Coding of the transcripts will take place through an iterative process, with data being grouped into themes drawn from idea codes to generate a ‘node tree of ideas’.

Primary outcome:The proportion of sick children referred from the private sector that completes the referral process (seen at higher health facilities), Table 2.

**Table 2 Tab2:** Period of evaluation and source of data for each endpoint

Endpoint	Source of data	Period of evaluation (start date – end date)
Primary endpoints:		
Uptake of referral advice	Referral forms Referral follow-up visits	October 2015 – September 2016
Secondary endpoints:		
Appropriate management of malaria, diarrhoea and pneumonia	Treatment record form	October 2015 – September 2016
Factors related to referral	Focus group discussions, KIs Household survey	October 2015 – September 2016

Secondary outcomes:Appropriate case management for malaria, pneumonia and diarrhea among children in the private sector.Factors which influence the referral or non-referral of sick children from the private sector.

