### Sample size estimation

The study will recruit 319 sick children per cluster and the total number of sick children to be recruited from all clusters will be 8910; adjusting for a 10 % loss to follow up and possible withdrawal of private outlets. This was based on assumption that the intervention will increase the primary outcome from 28 to 40 %, at a study power of 80 %, 5 % level of significance and a cluster correlation k, of 0.15; 20 clusters will be required. Ten (10) of them will be randomly allocated to the intervention and 10 to the control arm.

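### Untransformed primary analysis: the risk difference is weighted by cluster size, but the test is only called an unpaired t-test, so the p-value may not belong to the reported estimate and interval

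*Protocol article*

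**What the plan says.** All the relevant text is in the protocol article, Study outcomes and analytic methods, which adopts a cluster-level analysis because there are few clusters per arm.

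- **Estimate, untransformed branch.** The risk difference is formed "using a weighted average of the cluster proportions, with weights proportional to the sample size for each cluster". The reason given is unequal volume: "since consultation rates differ between drug shops/private clinics and clusters".
- **Interval, untransformed branch.** The "confidence intervals will be computed assuming separate estimates of the variances in the two study arms". No variance formula for the weighted means is given.
- **Log branch.** "If the data have been log transformed, this will be the ratios of the geometric means", and the interval is obtained, "if log transformed using an estimate of the pooled standard deviation of the log-transformed cluster summaries". No weights are mentioned.
- **Test.** "The null hypothesis that there is no intervention effect will be tested using an unpaired" t-test. The text does not say whether the test is weighted or which variance form it uses.

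The covariate-adjusted analysis and the other secondary outcomes refer back to these same methods. Under Sample size estimation, "Ten (10) of them will be randomly allocated to the intervention and 10 to the control arm", and the design assumes that "the intervention will increase the primary outcome from 28 to 40 %, at a study power of 80" per cent, with k = 0.15 and 319 sick children per cluster.

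**The concern.** Weights proportional to size make the arm summary Σnⱼpⱼ/Σnⱼ, which is the pooled proportion: every child counts equally. A plain two-sample t-test on cluster proportions compares Σpⱼ/10 between arms: every cluster counts equally. The two coincide only when clusters are the same size, and the plan justifies its weights by saying they are not.

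The text allows two readings of the test, and each has a cost.

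1. **Unweighted test.** The p-value belongs to a different contrast from the reported risk difference and interval. One can be significant while the other is not.
2. **Size-weighted test.** The three results then agree with each other. However, weights proportional to n are right only if a cluster proportion has variance proportional to 1/n, that is, with no between-cluster variation. The design itself assumes such variation through k.

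**Working it through.** **Inputs from the protocol article:** 10 clusters per arm, 28% v 40%, k = 0.15, 319 per cluster. A two-sided 5% level is assumed.

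**Assumed inputs:** cluster-size CV of 0.5 to 1.0, since none is given. A second cluster size of 40 is also used, because the primary denominator is referred children whereas 319 counts sick children. Cluster size is taken as independent of outcome.

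**Step 1. The design figure, for context.** With m = 319, c = 1 + (1.96+0.84)²[p₀(1−p₀)/m + p₁(1−p₁)/m + k²(p₀²+p₁²)]/(p₁−p₀)².
- The bracket is 0.2016/319 + 0.24/319 + 0.0225 × 0.2384 = 0.00675. So c = 1 + 7.85 × 0.00675/0.0144 = 4.68, or 5 clusters per arm rather than 10.
- Ten per arm gives about 99% power at k = 0.15. It gives about 80% at k of about 0.25.
- The mismatch in the sample size is a separate matter. It matters here only because disagreement between interval and test is rare when power is near 99%, so k = 0.25 is shown as well.

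**Step 2. Which weights suit which cluster size.** At 28% and k = 0.15 the between-cluster variance is (0.15 × 0.28)² = 0.00176.
- Within-cluster variance at 319 is 0.2016/319 = 0.00063. Between-cluster variance is 0.00176/(0.00176+0.00063) = 74% of the total, so near-equal weights are appropriate.
- Within-cluster variance at 40 is 0.2016/40 = 0.00504. The between-cluster share is 0.00176/(0.00176+0.00504) = 26%, so weights closer to size are appropriate.
- The weights n/(1+(n−1)ρ), with ρ = k²p/(1−p) = 0.0225 × 0.28/0.72 = 0.00875, adapt to both cases.

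**Step 3. Separate v pooled variances.** With 10 v 10 clusters, the pooled squared standard error is [(9s₁²+9s₀²)/18](1/10+1/10) = (s₁²+s₀²)/10, which is the separate-variance form. Only the degrees of freedom differ (18 v 9 to 18). By simulation this alone changes significance in 0.1% to 1.0% of trials.

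**Step 4. Simulation of the two readings.** Settings: 20,000 trials each, beta-binomial clusters, lognormal sizes. The interval is centred on the size-weighted difference and uses separate-arm variances of the cluster proportions.

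| Quantity | Setting | Result over size CV 0.5 to 1.0 |
|---|---|---|
| Interval v unweighted t-test disagree | 40 per cluster, k = 0.15, 28% v 40% | 11%, 17%, 21% (CV 0.5, 0.8, 1.0) |
| Same | 319, k = 0.15, 28% v 40% | 1.2%, 2.7%, 3.8% |
| Same | 319, k = 0.25, 28% v 40% | 10% to 17% |
| Same | 319, k = 0.15, no effect | 3.7% to 6.4% |
| Type I error, size-weighted t-test, 18 df | 319, k = 0.15 | about 7% to 10% |
| Type I error, weights n/(1+(n−1)ρ), true ρ | 319, k = 0.15 | about 5% |
| Type I error, unweighted t-test | 40 and 319 | about 5% |

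Over size CV 0 to 1.0, coverage of that interval is about 95% to 97% at 40 per cluster and 92% to 95% at 319. At 40 per cluster and CV 0.8, power is about 66% for the unweighted test and 76% with variance-based weights.

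In a wider set of runs (30 or 319 per cluster, k = 0.15 or 0.30), the weighted and unweighted risk differences differed on average by 0.8 to 2.2 percentage points at size CV 0.5. At CV 1.0 they differed by 1.5 to 4.1 points. The target difference is 12 points.

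**The case against.** The strongest reply is that the protocol never says the test is unweighted. Unpaired describes a two-sample layout. The test follows directly after a weighted estimate and an interval said to correspond to it, so a weighted test is not excluded, and a condensed article may leave the formula to a fuller document. A reader might infer that the plan prescribes an unweighted test, but the text does not establish that, and this part stands. It does not remove the problem, because carrying the stated weights into the test raises type I error at 319 per cluster. What the article fixes, weights proportional to size, is itself the difficulty on that reading.

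Size weighting also targets a legitimate quantity, the child-average effect, and the plan gives a reason for it. That stands too. The issue is the pairing with the test and the omission of between-cluster variance, not the choice of estimand.

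Three stronger readings are tempting but not supported:

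- **The separate-variance interval contradicts the test.** With 10 v 10 clusters it does so in at most about 1% of trials, and an unpaired t-test can itself use separate variances.
- **The whole primary analysis is incoherent.** In the log branch, the ratio of geometric means, the pooled SD of the log summaries and the t-test fit together.
- **The intervention distorts the weights by changing volume.** Referral training, subsidised drugs and placards make this plausible, but the documents give no volume figures and it has not been quantified.

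Finally, the larger disagreement rates depend on 40 referrals per cluster, which is an assumption. At the only cluster size stated, with k = 0.15 and the full effect, the rate is about 1% to 4%.

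**Conclusion.** The point holds for the untransformed branch. As written, either the p-value tests a different contrast from the estimate and interval, or the size weights enter the test and it no longer holds its 5% level.

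On the first reading the consequence ranges from small to material. It is small if about 319 children per cluster enter the primary denominator with k = 0.15 and the full effect. It is material if referrals per cluster are nearer 40, or if k is nearer 0.25. Interval coverage of about 92% to 97% at k = 0.15 is a modest departure from 95%, not a breakdown. On the second reading, type I error of about 7% to 10% at 319 per cluster is the main cost.

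All these figures rest on the assumed size CVs. With equal clusters the disagreement falls to 1% or less. The trial is not without a usable primary result, but the wording should be settled before the blinded analyst starts.

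**What to change.** State that the primary estimate, its 95% CI and its p-value come from one cluster-level analysis with one set of weights, and give the variance formula. Two options work:

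- **Equal weights for all three.** This is simple and holds the 5% level. The cost is precision when sizes vary, as in the 66% v 76% power comparison at 40 per cluster and size CV 0.8.
- **Regression of cluster proportion on arm, 18 df, weights n/(1+(n−1)ρ).** This suits both large and small clusters. The cost is that ρ must be estimated from 20 clusters. The roughly 5% type I error shown used the true ρ.

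Keep the size-weighted risk difference as a sensitivity analysis. With one set of weights and one reference distribution, interval and test cannot disagree. The change affects analysis wording only, not design or data collection. It should also apply to the adjusted and secondary analyses that refer back to this text.

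### Time from consultation to referral uptake is assigned methods built for cluster proportions, and times exist only for children who arrived, so the comparison conditions on the primary outcome

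*Protocol article*

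**What the plan says.** All of this is in the protocol article, section Study outcomes and analytic methods, except where stated.

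- The primary outcome is the proportion of referred children who complete referral, meaning that they are seen at a higher-level facility. Its denominator is all referrals, and the primary approach is intention to treat.
- The analysis starts from cluster proportions: "The proportion relating to this primary outcome will be calculated in each cluster". Arms are compared by risk differences, "using a weighted average of the cluster proportions, with weights proportional to the sample size for each cluster". For skewed data there is a log-scale alternative: "If the data have been log transformed, this will be the ratios of the geometric means".
- The test is also fixed: "The null hypothesis that there is no intervention effect will be tested using an unpaired" t-test. For covariate adjustment, "adjusted risk differences and 95 % CIs will be estimated as described above, replacing the cluster-level proportions with the covariate adjusted residuals".
- The paragraph then closes with "The above methods will also be used to analyse the other secondary outcomes", and among these it lists the "time between consultations at private outlets and uptake of referral at health facilities".

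The text gives no cluster summary for a duration, no follow-up limit for arrival, and no rule for referred children who never arrive. Sample size estimation assumes that completion rises from 28% to 40%.

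**The concern.** There are two problems, one behind the other.

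First, the assigned method does not fit the outcome. A time has no cluster proportion, and a difference between arms in time is not a risk difference. An analyst following the paragraph literally has nothing to compute.

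Second, the obvious repair brings in selection. An analyst would probably replace the cluster proportion with the mean, or mean log, of the observed times. A child who never arrives has no uptake time, so the average covers completers only. Completion is what the intervention is meant to change, so the analysis conditions on a post-randomisation event that is itself the primary outcome. Randomisation no longer makes the two groups comparable. The denominator also departs from the all-referrals basis of the primary outcome.

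At stake is a published statement on timeliness. The Background gives timely arrival at an appropriate level of care as part of the rationale. A completers-only comparison could report slower or faster referral when no child's time had changed.

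**Working it through.** The plan states no figure for this outcome, so there is none to reproduce. The only trial inputs needed are the assumed completion proportions in Sample size estimation: p0 = 0.28 (control) and p1 = 0.40 (intervention).

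**Step 1: who has a time.** Referred children without a value:
- control: 1 − 0.28 = 72%
- intervention: 1 − 0.40 = 60%

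The share with missing values differs by 12 percentage points between arms, and that difference is the planned effect itself.

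**Step 2: make-up of the intervention completers.** Net additional completers make up (0.40 − 0.28)/0.40 = 12/40 = 30%. This assumes that the same kinds of children are referred in both arms and that every child who would complete under control would also complete under the intervention.

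**Step 3: effect on a completers-only mean.** Suppose the intervention changes nobody's time. Set the mean among children who would complete anyway to 1 unit, and let the additional completers average r units. The control mean is 1. The intervention mean is

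(0.28 × 1 + 0.12 × r)/0.40 = 0.7 + 0.3r.

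The values of r are assumptions, shown as a range because the documents give no information on arrival times.

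| r | Intervention mean (control = 1.00) | Share of simulated trials with p < 0.05 |
|---|---|---|
| 0.5 | 0.85 | about 28% |
| 1 | 1.00 | about 4% |
| 2 | 1.30 | about 62% |
| 3 | 1.60 | about 97% |

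The last column comes from 2,000 simulated trials per row. Each had 10 clusters per arm, 60 referrals per cluster (assumed), between-cluster coefficient of variation 0.15 for completion, exponential times (assumed), and an unpaired unequal-variance t-test on unweighted cluster mean times. Mean times were not allowed to vary between clusters. Real variation of that kind would pull these rates down, so they show only that the artefact can reach significance. The means in the second column do not depend on the simulation.

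**Step 4: the log scale does not remove it.** If log times are averaged over completers, and r is now the ratio of geometric mean times, the intervention-to-control ratio is r^0.3. That gives 0.5^0.3 = 0.81, 1^0.3 = 1.00, 2^0.3 = 1.23 and 3^0.3 = 1.39. The pattern is the same, with smaller departures above 1.

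**Step 5: the same scenario with all referred children in the denominator.** Let F(t) and G(t) be the proportions arrived by time t among the would-be-anyway and the additional completers. The proportion of all referrals seen by t is 0.28F(t) in control and 0.28F(t) + 0.12G(t) in intervention. The difference is 0.12G(t), which lies between 0 and 12 points. It cannot turn against the intervention when no child is slower. It is 0 if all additional completers arrive after the window, and it reproduces the primary result if all arrive within it.

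**The case against.** The strongest reply is that the paragraph describes a general cluster-level approach. Summaries per cluster, log transformation for skewness, a ratio of geometric means, a t-test and residual adjustment can all be carried over to times. A reader might infer that the comparison is wholly undefined. That goes too far: only the cluster proportion and the risk difference have no meaning for a duration. The t-test or the geometric-mean ratio could be computed on cluster times, although the text does not say so, and the selection problem would remain.

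It can also be said that completers-only averaging is not written anywhere. The other timing outcome, care seeking within 24 h of symptom onset, is already a proportion, and the time to uptake might be dichotomised in a fuller document. This is fair, and it is why the second problem is stated conditionally. But the article describes the outcome as a time, assigns it a method, and gives no rule for children without a value. That is a stated mismatch, not merely an omitted detail.

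A reader might further infer that the intervention will look slower. The documents do not support a direction. That reading needs the additional completers to be later arrivals, and nothing in the article says when children arrive. With faster additional completers the artefact favours the intervention.

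Finally, the outcome ranks low. It is introduced among the other outcomes, is grouped with the secondary outcomes only in the analysis paragraph, and is absent from the objectives, the secondary outcome list and Table 2. Completion is reported alongside it, so readers would see how many children arrived. This stands and lowers the priority.

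**Conclusion.** The point holds in this form. The stated proportion and risk difference cannot be applied to the time to uptake. A comparison of cluster mean or log times would rest on 28% of control and 40% of intervention referrals, selected by the primary outcome.

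Under the plan's completion figures, a completers-only mean moves by the factor 0.7 + 0.3r with no change in any existing completer's time: 0.85 to 1.60 for r from 0.5 to 3. The sign is unknown, and the bias disappears only if the additional completers' times match the others'. This rests on the 28% and 40% assumptions, on similar referred populations in the two arms, and on illustrative values of r. No single corrected figure exists. The issue is lower priority and does not touch the primary analysis.

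**What to change.** Redefine the cluster summary for this outcome as the proportion of all referred children seen at the referral facility within a prespecified window after the consultation, with non-arrivals counted as not seen. The stated cluster-level methods then apply unchanged. The window should be chosen without sight of results by arm and justified for this interval. The 24 h cut-off already in the article concerns symptom onset to attendance at the private outlet, so it does not carry over automatically.

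Alternatively, use a time-to-event analysis of all referred children, with non-arrivals censored at a stated follow-up limit and with allowance for clustering that suits 20 clusters. In either case, report time among completers descriptively only.

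Costs:
- A single window loses some information on timing.
- Arrival dates must be captured. It is tempting to assume that they already are, but the data list under Training of private providers names neither a consultation nor an arrival date, and the community follow-up is described as checking whether referral was taken up, not when. The date is needed on the referral form and at the follow-up visit, including for children who arrive without a form, who would otherwise be misclassified as not seen.
- Study status reports that the intervention is already running, so for children already enrolled the dates may have to be recovered from existing records.

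One limitation remains. The intervention trains providers in whom to refer, so the referred children may themselves differ by arm. Neither option removes this, and the report should say so.
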